## Abstract

**Background:**

Rectal Cancer is a common malignancy. The current treatment approach for patients with locally advanced rectal cancer involves neoadjuvant chemoradiotherapy followed by surgical resection of the rectum. The resection can lead to complications and long-term consequences.

A clinical complete response is observed in some patients after chemoradiotherapy. A number of recent studies have shown that patients can be observed safely after completing chemoradiotherapy (without surgery), provided clinical complete response has been achieved. In this approach, resection is reserved for cases of regrowth. This is called the watch and wait approach. This approach potentially avoids unnecessary surgical resection of the rectum and the resulting complications. In this study, we will prospectively investigate this approach.

**Methods:**

Adult patients with a diagnosis of rectal cancer planned to receive neoadjuvant long course chemoradiotherapy (± subsequent combination chemotherapy) will be consented into the study prior to commencing treatment. After completing the chemoradiotherapy (± subsequent combination chemotherapy), based on the clinical response, subjects will be allocated to one of the following arms: subjects who achieved a clinical complete response will be allocated to the watch and wait arm and others to the standard management arm (which includes resection). The aim of the study is to determine the rate of local failure and other safety and efficacy outcomes in the watch and wait arm. Patient reported outcome measures and the use of biomarkers as part of the clinical monitoring will be studied in both arms of the study.

**Discussion:**

This study will prospectively investigate the safety of the watch and wait approach. We will investigate predictive biomarkers (molecular biomarkers and imaging biomarkers) and patient reported outcome measures in the study population and the cost effectiveness of the watch and wait approach. This study will also help evaluate a defined monitoring schedule for patients managed with the watch and wait approach. This protocol covers the first two years of follow up, we are planning a subsequent study which covers year 3–5 follow up for the study population.

Trial registration.

Name of the registry: Australia and New Zealand Clinical Trials Registry (ANZCTR). Trial registration number: Trial ID: ACTRN12619000207112 Registered 13 February 2019,https://www.anzctr.org.au/Trial/Registration/TrialReview.aspx?id=376810

**Supplementary Information:**

The online version contains supplementary material available at 10.1186/s12885-022-09304-x.

## Background

Rectal Cancer is a common malignancy [1], comprising one third of all colorectal cancer cases [2]. In patients with non-metastatic locally advanced rectal cancer (stage II or III), the current standard management approach involves pre-operative (neoadjuvant) chemotherapy and radiotherapy followed by total mesorectal excision. Neoadjuvant chemoradiotherapy (CRT) is also recommended in patients with extramural vascular invasion (EMVI)—detected by magnetic resonance imaging (MRI)—as EMVI has been identified as a risk factor that predicts relapse, regardless of T and N stage.[3] Surgical resection of the rectum involves a mortality risk and can lead to considerable morbidity, including serious complications such as anastomotic leak.[4, 5] Other possible complications following rectal cancer resection include sexual and urinary dysfunction, which can occur in up to 25% of patients treated by radical surgery, even with meticulous nerve-sparing procedures and in highly specialized centres.[6].

Preoperative CRT can reduce the size of the primary tumour and the depth of tumour penetration and can potentially sterilize the involved lymph nodes. Large randomized studies have established preoperative CRT as the preferred treatment option for patients with stage II or III rectal cancer.[7–11] More recently, studies have shown that the addition of combination chemotherapy to either a short course of radiotherapy or standard long course concurrent CRT before surgery, can improve outcomes.[12–14] This approach is called total neoadjuvant therapy (TNT).

In some patients, preoperative CRT can lead to pathological complete response. Pathological complete response is established when no viable malignant cells are found in the resected surgical specimen. Patients who achieve pathological complete response have better outcomes.[15] Pooled analysis of data shows the rate of pathological complete response to be approximately 15% with CRT and 30% with TNT.[16] Establishing pathological complete response requires examination of the surgical specimen. In patients who have not had surgery, clinical complete response (cCR) is used as a surrogate for pathological complete response. cCR is established when no malignancy is found on clinical examination, imaging, endoscopy (sigmoidoscopy) and biopsy.[15, 17] Surgery may not be necessary in these patients. This approach is known as watch and wait.

We designed the current study to prospectively investigate the safety of the watch and wait approach and to study multiple secondary outcomes which have not been studied adequately in the past. These secondary outcomes include biomarker studies, patient reported outcome measures (PROMs) and cost effectiveness.

Further research is necessary to discover and validate diagnostic biomarkers of cCR and predictive biomarkers of local failure. In this study we are aiming to investigate a multitude of biomarkers, including imaging biomarkers, non-coding RNAs [25, 26], circulating tumour DNA (ctDNA) [27–29], circulating methylated DNA [30, 31], tumour infiltrating lymphocytes (TILs) [32–34], organoids [35] and gut microbiome [36–38]. PROMs have not been studied in detail in this group of patients. In this study, we will thoroughly explore the burden of long-term side effects as well as other quality of life measures using validated questionnaires. We will use specific tools to investigate bowel related quality of life measures, including incontinence and bowel function. We will also study fear of cancer recurrence in the study population. Like other cancer survivors, the current study population experience ongoing issues during the survivorship continuum, we are aiming to assess these issues and the supportive care needs of the study population. Cost effectiveness evidence has not been thoroughly measured and reported for the watch and wait approach in patients with rectal cancer. The scarcity of resources mandates that health care investments be made in the most cost-effective manner. Health economics evaluation is a method whereby benefits and costs of alternative treatment options can be considered to aid decision-makers in prioritising and allocating health resources.[39].

## Methods

### Aims and objectives

#### Primary objectives

To determine the safety and efficacy of the watch and wait approach, by measuring the following endpoints in the watch and wait arm:Co-Primary endpoint 1: The ‘two-year local failure rate’Co-Primary endpoint 2: The rate of rectal preservation

Secondary objectives:To determine the safety of the watch and wait strategy by measuring the following endpoints (in the watch and wait arm):The ‘two-year local regrowth rate’The ‘two-year distant metastasis rate’The overall survivalThe ‘incurable disease-free survival rate’ (recurrent cancer that cannot be surgically excised with the intention of achieving a cure)Evaluate the role of biomarkersPlasma and tumour biopsy biomarkers (non-coding RNAs, methylated DNA), TILs, organoids and gut microbiome:i)To predict cCR (in both arms)ii)To identify residual disease, micrometastases and recurrence risk (in both arms)iii)As prognostic biomarkers (in both arms)Imaging biomarkers (mrTRG, diffusion and T2 signs)i)To predict sustained cCRPROMs (in both arms)Quality of life (quality of life and health related quality of life)Bowel related quality of lifeFear of cancer recurrenceSupportive care needsTo evaluate a defined monitoring schedule in the watch and wait armCost effectiveness analysis: (both arms)

### Design

This is a Longitudinal Cohort Study.

Eligible subjects, after consent/registration, will complete CRT and then based on response will be allocated to one of the two study arms.

### Subect population

#### Target population

Adult patients with a diagnosis of locally advanced rectal cancer who are going to receive combined long course CRT (± subsequent combination chemotherapy).

#### Study setting

Participants will be accrued from hospitals and outpatient clinics in Australia. List of s study sites can be found through: https://www.anzctr.org.au/

Inclusion criteria.Age ≥ 18 yearsBiopsy proven locally advanced rectal adenocarcinoma:i)Locally advanced disease defined as: T3 N0-2, T1-2 N1-2 [Based on AJCC UICC 2017]Subject to undergo long course neoadjuvant CRT (± subsequent combination chemotherapy) based on a multidisciplinary meeting recommendationConsidered suitable for long course pelvic radiation therapyConsidered suitable for surgeryConsidered suitable for MRIWilling and able to comply with all study requirements, including treatment and follow up assessmentsSigned, written informed consent

Exclusion criteria.Presence of metastatic disease (M1)T4 disease based on AJCC 2017Local recurrence of previously treated rectal cancerPrevious pelvic radiotherapyContraindication to fluoropyrimidine chemotherapyHistory of another malignancy:i)Patients with a history of adequately treated carcinoma-in-situ, basal cell carcinoma of the skin, squamous cell carcinoma of the skin, or superficial transitional cell carcinoma of the bladder are eligible. Patients with a history of other malignancies are eligible if they have been continuously disease free for at least 5 years after definitive primary treatment.Concurrent illness, including severe infection that may jeopardize the ability of the patient to undergo CRT with reasonable safetyPresence of any psychological, familial, sociological or geographical condition potentially hampering compliance with the study protocol including CRT and/or follow-up schedulePregnancy or lactation

### Study procedures

#### Screening

Written informed consent (model consent form: supplementary file-1) will be obtained before screening procedures are undertaken. Participants will have pretreatment sigmoidoscopy. Pre-treatment specimens (including biopsy, plasma and stool specimens) will be collected within this time-frame. If all screening procedures are performed and eligibility is confirmed, the patient will be registered for the trial.

#### Registration

Subjects must meet all the inclusion criteria and none of the exclusion criteria to be eligible for this study. Subjects must be registered before entering the study. Registration should be done only after all screening assessments have been performed.

Run-in phaseParticipants receiving only CRT:i)Run-in phase post CRT – week 8–10: patients will have a clinical assessment and endoscopy (sigmoidoscopy) and CT scan (run-in investigations) between week 8—10 post CRT. If there is no evidence of residual cancer found in the run-in phase investigations, subjects will have an MRI.ii)Allocation visit – week 8–10: At the allocation visit all investigations during the run-in phase will be evaluated. Patients who have achieved cCR will be allocated into the watch and wait arm. All other patients will be allocated to standard management arm.Participants receiving TNT:i)Run-in phase post TNT – week 2–3: patients will have a clinical assessment and endoscopy and CT scan (run-in investigations) between week 2–3 after the last dose of TNT. If there is no evidence of residual cancer found in the run-in phase investigations, subjects will have an MRI. If patients are required or decide to stop the doublet chemotherapy earlier than the recommended number of cycles, they will proceed to tumour response assessment 2–3 weeks after the last dose of doublet chemotherapy and allowing a minimum of 8 weeks post CRT before the response evaluation takes place.ii)Allocation visit (participants receiving TNT) – week 2–3 after the last dose of doublet chemotherapy. At the allocation visit all investigations during the run-in phase will be evaluated. Patients who have achieved cCR will be allocated into the watch and wait arm. All other patients will be allocated to standard management arm.

### Treatment Plan

#### Administration of study treatments

RadiotherapyRadiation therapy is to start with concurrent chemotherapy.Simulation with bladder and bowel protocol.Immobilisation with ankle and knee supports.Anal marker is optional.Fusion of MRI preferred with planning CT scan at 2–3 mm slices through relevant area.Volumetric modulated arc therapy (VMAT)/Intensity modulated radiotherapy (IMRT) is the preferred technique with a simultaneous integrated boost.Target volumes:Primary – Gross tumour volume of primary (GTV-P) = gross diseaseClinical target volume of primary (CTV-P) = GTV-P plus adequate margin superior and inferior (2cm), radially (1cm but discretion of clinician). Planning target volume of primary (PTV-P) = CTV-P + 0.5 -1.0 cm. NodesGross tumour volume of lymph nodes (GTV-N) = gross nodal disease. Clinical target volume of lymph nodes (CTV-N) = GTV-N plus mesorectum, internal iliac, presacral and other appropriate nodal areas as designated by radiation oncologist e.g., if anal canal involvement, the external iliac, obturator, inguinal and ischiorectal fossa nodes may be treated. Planning target volume of lymph nodes (PTV-N) = CTV-N plus 0.5- 0.7 cm.Dose prescription: PTV-P and PTV-N = 45 Gy /25F / 1.8 Gy per fractionSimultaneous integrated boost to gross disease for total of 50 Gy /25F.A one phase technique to 50.4 Gy /28F or 50 Gy /25F is optional.Image verification: cone-beam computed tomography (CBCT) day1 to day 3 then weekly as a minimum.

### Chemotherapy

Neoadjuvant chemotherapy will be given concurrently with radiation and will comprise of a single agent fluoropyrimidine regimen: intravenous 5-FU: 225 mg/m2 continuous IV infusion via pump during the radiation therapy course, OR Oral capecitabine—825 mg/ m2 PO BD (days 1–5, excluding weekend).

Proceeding with ‘adjuvant’ chemotherapy (i.e., chemotherapy after completion of concurrent CRT) in the watch and wait arm is based on treating clinicians’ decision. In the watch and wait arm, it is recommended that patients receive adjuvant doublet chemotherapy with a fluoropyrimidine and oxaliplatin (for a total of 3 months (6 cycles of FOLFOX or 4 cycles of CAPOX) if the patient did not receive TNT and they are otherwise considered suitable for chemotherapy.

For patients considered suitable for TNT, combination doublet chemotherapy will commence 10–14 days after completion of CRT. This will consist of either 8 cycles of FOLFOX, administered on 2-week cycles, or 6 cycles of CAPOX, administered on 3-week cycles. Doublet chemotherapy dosed as per local and eviQ guidelines (eVIQ guidelines are available at https://www.eviq.org.au). If patients are required or decide to stop the doublet chemotherapy earlier than the recommended number of cycles, they will immediately proceed to tumour response assessment, allowing a minimum of 8 weeks post CRT before the response evaluation takes place.

Chemotherapy dose modifications are in accordance with local and eviQ guidelines.

Concomitant medications/treatments during chemotherapy:Metronidazole and warfarin are best avoided during CRT with 5-FU and must be used with caution. Warfarin is best avoided during CRT with capecitabine, and must be used with cautionFolic Acid should not be used during CRT with 5-FU.If necessary, antibiotics can be used during CRT, but their use must be documented and captured in the database for evaluation.

### Assessment plan

Schedule of assessments is summarized in Table 1. Schedule of PROMs is summarized in Table 2.Timing of the monitoring visits will be calculated from the allocation visit.The watch and wait arm: monitoring visits: monitoring visits and procedures to be scheduled according to the assessment timetable (± 2 weeks)The standard management arm: PROMs questionnaires to be completed according to the to the assessment timetable (± 2 weeks)Follow-up after stopping the study: If a patient wishes to stop the study visits, they will be requested to allow their ongoing health status to be periodically reviewed via continued study visits or phone contact or from their general practitioner, or medical records, state-based cancer registries and/or the national mortality registry.For patients who have been lost to follow-up, Medicare may be used to provide updated contact information and/or hospitalisations and the national registry may be used to collect mortality information.

### Outcomes, endpoints and other measures

#### Safety and efficacy

Two-year local failure rate (Co-Primary Endpoint)This endpoint will be measured in the watch and wait arm only. It is defined as local recurrence (i.e., recurrence in the region of the rectum, mesorectum and adjacent lymph nodes) that cannot be resected with clear margins.Metastatic disease:Metastatic disease in the presence of local recurrence is considered ‘local failure’Metastatic disease in the absence of local cancer recurrence is not considered ‘local failure’The rate of rectal preservation (Co-Primary endpoint)This endpoint will be measured in the watch and wait arm only. It is defined as the rate of organ (rectal) preservation at two years.

Rate of incurable-disease free survival (incurable-disease or death)Defined as the interval from date of registration to the date of first evidence of ‘local failure’ or ‘distant metastatic disease’ or death, whichever occurs firstOverall survival (death from any cause)Overall survival is defined as the interval from the date of registration to date of death from any cause, or the date of last known follow-up alive.Two-year local recurrence rateLocal Recurrence is defined as evidence of recurrent disease within the pelvis, found by examination, endoscopy or imaging (CT or MRI). Biopsy and pathological confirmation are encouraged if technically possible and safe.Two-year distant recurrence rateDistant Recurrence is defined as evidence of recurrent disease other than local recurrence, found by imaging or on examination.

Translational research (biomarkers).

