### Statistical considerations

#### Sample size

The sample size is determined by utilizing the precision of the expected rate of local failure for patients with cCR after CRT. Based on available literature, the failure rate by 3-years is assumed to be 5%. A sample of 50 participants with cCR will be required to allow for 47 assessable participants (considering 5% potential drop out). This sample size calculation provides a precision of ± 10% with 95% confidence for the estimate of 5% local failure rate. Expecting 20% rate of cCR, this will translate into a total of 250 participants to be enrolled into the study to result in 50 participants in the watch and wait arm. (50 participants in the watch and wait arm and 200 in the standard management arm).

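### Incurable-disease-free survival counts every distant metastasis as an event, although the objective limits it to recurrence that cannot be excised for cure

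*Protocol article*

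**What the plan says.** The endpoint appears in two places in the Protocol article.

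- **Aims and objectives, secondary objectives.** The incurable disease-free survival rate is one of four secondary safety endpoints in the watch and wait arm. A parenthesis gives its meaning: "recurrent cancer that cannot be surgically excised with the intention of achieving a cure".
- **Outcomes, endpoints and other measures, Safety and efficacy.** The label keeps that intent: "Rate of incurable-disease free survival (incurable-disease or death". The definition beneath it runs from registration to "first evidence of ‘local failure’ or ‘distant metastatic disease’ or death", whichever is first.

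The components are defined in the same section. Local failure is local recurrence "that cannot be resected with clear margins". Distant recurrence is any recurrent disease other than local recurrence, found on imaging or examination, and whether it can be resected plays no part. A further rule says "Metastatic disease in the presence of local recurrence is considered ‘local failure", paired with one saying that metastasis without local recurrence is not local failure.

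**The concern.** The objective and the label promise a measure of incurable disease. The operational definition delivers a different event set, because a distant metastasis is an event as soon as it is seen, whether or not it can be excised for cure. The two rules give opposite answers for a patient whose metastasis is excised for cure.

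This affects interpretation. The endpoint is listed as a safety measure of watch and wait. If it is reported under its present name, some patients who were treated with curative intent and remained disease-free will appear as incurable. A reader would have no way to tell this from the endpoint itself. The arm is planned at only 50 patients, so each such patient moves the rate by 1/50 = 2 percentage points.

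**Working it through.** **Step 1. Is there a figure to reproduce?** No. The protocol gives no expected rate, precision or sample size for this endpoint. The Sample size section rests on local failure alone: "A sample of 50 participants with cCR will be required to allow for 47 assessable participants (considering 5% potential drop out". Those numbers do reproduce (47 / 0.95 = 49.5, rounded up to 50; 50 / 0.20 = 250 enrolled), but none depends on this point.

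**Step 2. Compare the event sets for a patient in the watch and wait arm.**

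| Patient's course | Event under the objective's wording? | Event under the outcomes definition? |
|---|---|---|
| Local recurrence not resectable with clear margins | Yes | Yes |
| Local recurrence alone, resected with clear margins | No | No |
| Metastasis not excisable for cure | Yes | Yes |
| Metastasis alone, excised for cure, no later event | **No** | **Yes** |
| Metastasis excised for cure, later incurable relapse or death | Yes, at the later date | Yes, at first evidence of metastasis |
| Death | Yes (through the label) | Yes |

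The definitions disagree on status in the fourth row and on date in the fifth. Every event under the objective's wording is also an event under the outcomes definition, at the same time or sooner.

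**Step 3. Direction.** Because one event set contains the other, the event-free rate under the outcomes definition cannot exceed the rate under the objective's wording. At two years it is lower if at least one patient falls in the fourth row.

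**Step 4. Size, as an illustration.** Let d be the share of patients with metastasis by two years and s the share of these excised for cure. Neither is in the documents; both are assumptions. The largest possible difference in the two-year rate is d × s, and in patients it is 50 × d × s.

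| d (assumed) | s = 10% | s = 40% |
|---|---|---|
| 5% | 0.5 points (0.25 patients) | 2.0 points (1.0 patient) |
| 10% | 1.0 point (0.5 patients) | 4.0 points (2.0 patients) |
| 15% | 1.5 points (0.75 patients) | 6.0 points (3.0 patients) |

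If s were as high as 50%, the top corner would be 15% × 50% = 7.5 points (3.75 patients). These are upper limits for each pair of assumptions. A patient whose metastasis is excised may still have local failure, incurable relapse or death within two years, and then counts under either wording.

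**The case against.** The strongest reply is that the broad definition is defensible. First evidence of metastasis is easy to date, needs no judgement and errs on the cautious side in a safety study. Local recurrence, distant recurrence and overall survival are also reported separately, so a careful reader can see the components. The endpoint is secondary, and neither the sample size nor the stopping rule uses it. All of this stands. It supports the broad event set as a choice, but it does not support calling that set incurable disease, or leaving an objective that says something narrower.

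Three stronger readings are tempting, and the documents do not support them.

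- *The co-primary local failure definition is wrong in the same way.* A reader might infer this, because a resectable regrowth with any metastasis counts as local failure. But the outcomes section gives explicit paired rules for metastasis with and without local recurrence. They read as a deliberate, cautious extension and can be applied without ambiguity. The Background uses local failure for unsalvageable local recurrence when describing an external series; it does not say how that series classed patients with both. Nor can the effect be gauged by taking 5% of 47 as the expected two-year count, because the plan says "the failure rate by 3-years is assumed to be 5" percent, which is a three-year figure.
- *The endpoint merely duplicates the distant metastasis rate.* It is a time-to-first-event composite that adds local failure and death. Overlap with one of its components is normal.
- *The definition prevents the trial from showing whether deferring surgery causes incurable disease.* Allocation is by response, not by randomisation, so no event definition would let the watch and wait arm establish that.

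**Conclusion.** The point holds for the secondary endpoint. The objective and the label describe incurable disease; the event list counts any distant metastasis; nothing else in the document reconciles them. The direction follows from the text alone: the reported rate is the same as or lower than the one the objective describes. The size does not. Under assumed metastasis rates of 5% to 15% and curative excision of 10% to 40% of cases, at most about 0.5 to 6 percentage points are affected, or 0.25 to 3 of 50 patients. No stated figure changes. What changes is what the endpoint can be said to show, and the correction is cheap.

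**What to change.** Reconcile the secondary objectives with the Safety and efficacy definition. There are two ways.

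1. **Preferred: narrow the event.** Limit the distant component to metastasis recorded as not excisable with curative intent, dated at that decision. Count a later incurable relapse after a curative excision when it occurs. Keep any distant metastasis as the separate endpoint that already exists.
2. **Otherwise: rename it.** Call it survival free of local failure or distant metastasis, reword the objective to match, and do not report it as incurable disease.

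The first option costs one case report form item with a date and a named decision-maker. Excisability is a judgement, and the protocol does not say that it is recorded: the multidisciplinary meeting is mentioned only for the recommendation of chemoradiotherapy. The second option costs wording only, but gives up the question that the objective asks.

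Leave the co-primary local failure definition and the stopping rule (3 cases in the first 15, 5 in the first 30) unchanged. Narrowing local failure would also make that safety boundary harder to reach. Under the first option, a patient with local recurrence and an excisable metastasis would still enter the composite through local failure. Reporting local failures that count only because of concurrent metastasis as a separate component would make that visible, and no more is needed.

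### Overall and incurable-disease-free survival of the watch and wait arm are counted from registration, which builds in about 3 to 6.5 months in which no event is possible

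*Protocol article*

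**What the plan says.** Three parts of the protocol article bear on this.

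- **Time origin (Safety and efficacy).** "Overall survival is defined as the interval from the date of registration to date of death from any cause". Incurable-disease-free survival is "Defined as the interval from date of registration to the date of first evidence of ‘local failure’ or ‘distant metastatic disease’ or death", whichever comes first.
- **Population (secondary objectives, listed after Primary objectives).** Both endpoints belong to the first secondary objective: "To determine the safety of the watch and wait strategy by measuring the following endpoints (in the watch and wait arm".
- **When that arm comes into being (Design; Registration).** "Eligible subjects, after consent/registration, will complete CRT and then based on response will be allocated to one of the two study arms". At the allocation visit, "Patients who have achieved cCR will be allocated into the watch and wait arm"; everyone else goes to standard management.

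The visit calendar has a different origin. Under Assessment plan, "Timing of the monitoring visits will be calculated from the allocation visit", and Table 1 runs from month 0 at allocation to month 24.

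Statistical analysis plans Kaplan-Meier or cumulative incidence curves and formal comparisons between groups by logrank, Cox, Gray and Fine and Gray methods. It says that all enrolled patients are included. It mentions no landmark, delayed entry or time-dependent arm.

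On the event itself, the secondary objectives explain incurable disease as "recurrent cancer that cannot be surgically excised with the intention of achieving a cure". The definition under Safety and efficacy counts distant metastatic disease without that limit.

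**The concern.** A patient who dies before the allocation visit, or whose cancer is detected at the run-in, cannot be in the watch and wait arm. For members of that arm, the time from registration to allocation therefore carries no risk of either endpoint (guaranteed or immortal time). Counting it as follow-up lifts the survival curve at every fixed time.

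The lift is larger after total neoadjuvant therapy than after chemoradiotherapy alone, because allocation comes later. The arm's estimate then depends on its treatment mix as well as on the safety of watch and wait. These endpoints are listed as measures of the safety of the strategy, and this effect makes it look safer.

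**Working it through.** **1. Time from registration to allocation.** The protocol states no figure for this, so it is summed from the schedule. Inputs:

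- Radiotherapy of 25 or 28 fractions (Treatment Plan). At an assumed 5 fractions a week this is 5.0 or 5.6 weeks.
- Chemoradiotherapy only: allocation 8-10 weeks after chemoradiotherapy (Registration).
- Total neoadjuvant therapy: doublet chemotherapy starts 10-14 days after chemoradiotherapy (1.4-2 weeks), as 8 two-week or 6 three-week cycles (Chemotherapy). Allocation is 2-3 weeks after the last dose (Registration). The last dose is assumed to fall at week 14 (start of the eighth two-week cycle) at the earliest and about week 17 (day 14 of the sixth three-week cycle) at the latest.

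| Pathway | Sum (weeks) | Weeks | Months |
|---|---|---|---|
| Chemoradiotherapy only, shortest | 5 + 8 | 13.0 | 3.0 |
| Chemoradiotherapy only, longest | 5.6 + 10 | 15.6 | 3.6 |
| Full total neoadjuvant therapy, shortest | 5 + 1.4 + 14 + 2 | 22.4 | 5.2 |
| Full total neoadjuvant therapy, longest | 5.6 + 2 + 17 + 3 | 27.6 | 6.3 |

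If the end of the last three-week cycle (week 18) is taken instead of the last dose, the longest case is 28.6 weeks (6.6 months). If doublet chemotherapy stops early, the eight-week minimum after chemoradiotherapy gives a floor of 5 + 8 = 13 weeks. The gap from registration to the start of chemoradiotherapy is not stated and adds to every row.

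An estimate at 24 months from registration therefore covers at most about 24 - 3.0 = 21 months of watch and wait, and only 24 - 6.6 = 17.4 months in the longest case.

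**2. Effect on a 24-month estimate.** Let g be the guaranteed months and S the true 24-month value counted from allocation. With a constant hazard after allocation, the registration clock reports

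S_reported = S^((24 - g)/24).

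The protocol gives no expected survival, so S is assumed:

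| Assumed S | 13.0 weeks | 15.6 weeks | 22.4 weeks | 27.6 weeks |
|---|---|---|---|---|
| 95% | 95.6% (+0.6) | 95.7% (+0.7) | 96.1% (+1.1) | 96.3% (+1.3) |
| 85% | 86.7% (+1.7) | 87.1% (+2.1) | 88.0% (+3.0) | 88.7% (+3.7) |

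At 28.6 weeks the shifts are +1.3 and +3.9 points.

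**3. Comparison between arms.** Suppose both groups have the same hazard, but the comparator is at risk from registration. The crude rate in watch and wait over 24 months is its events divided by its person-time, including the g event-free months. With hazard h = -ln(S)/24 and e = 1 - exp(-h(24 - g)), the ratio to the true rate is e / [h(g + e/h)]. For S of 85-95% this is about 0.87 at g = 3 and 0.74-0.75 at g = 6, where the truth is 1. This is an upper illustration: if the standard arm also contains only patients who reached allocation, its members had to survive that time too, and much of the effect on overall survival cancels.

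**4. The event definition.** Counting resectable metastases as events lowers incurable-disease-free survival. If 8-10% of the arm have distant recurrence and 20-40% of these are resectable (both assumed), the difference is 8% × 20% = 1.6 points to 10% × 40% = 4.0 points. Set against the clock effect at 85%, the net lies between 1.7 - 4.0 = -2.3 and 3.7 - 1.6 = +2.1 points.

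**The case against.** The strongest defence is that registration is the right origin for this design. The Discussion explains that patients are enrolled before chemoradiotherapy to reduce selection bias. That holds for the whole enrolled cohort, and the fix keeps it there. It does not hold for an arm defined by a response observed months later.

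The effect is also modest. With 50 watch and wait patients, the simple 95% half-width is 1.96 × √(0.85 × 0.15/50) = 9.9 points at 85% and 6.0 points at 95%, so the shift is well inside sampling error. That stands and bears on severity. The shift is nevertheless systematic and easily avoided.

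Four stronger readings are tempting, and the document does not support them.

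- *Early deaths fall in the standard arm by construction.* Arms are assigned at the allocation visit, so a patient who dies before it is, on the wording, in neither. All enrolled patients are to be analysed, but where such a patient is counted is not said. Metastases found at run-in do go to the standard arm.
- *The primary and recurrence endpoints share the fault.* Local failure, rectal preservation, local recurrence and distant recurrence are given no registration clock. The sample size and stopping rule rest on local failure and are untouched.
- *Two-year survival is misreported and late events are lost.* The two-year label is not attached to overall or incurable-disease-free survival. Events found at the month-24 visit, about 27-30 months from registration, stay on the curve and in any logrank or Cox analysis. Only a point estimate at 24 months from registration would miss them. Such an estimate is a natural one, given two years of follow-up, but it is not specified.
- *Incurable-disease-free survival is too high overall.* The event definition pulls the other way, and step 4 shows that the net sign is open.

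In addition, Statistical analysis names progression-free, local control and overall survival, not incurable-disease-free survival. The risk to comparisons is therefore explicit for overall survival only.

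**Conclusion.** The point holds. Both survival endpoints start before the arm they describe exists, and nothing in the stated analysis corrects for it. The built-in event-free time is at least 3.0-3.6 months after chemoradiotherapy alone and about 5-6.5 months after full total neoadjuvant therapy. The direction of the clock effect is certain. Its size, roughly 1 point at 95% and 2-4 points at 85%, rests on a constant hazard and on assumed survival values. Bias in the comparison between arms is possible but cannot be sized from the document.

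The disagreement over resectable metastases is real but is a separate matter of event definition. It does not make the time-origin point more serious. Both endpoints are secondary, so this should be fixed before analysis; it is not a threat to the trial's main conclusion.

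**What to change.** - **Time origin.** Under Safety and efficacy, state that for results by arm and for comparisons between arms, overall and incurable-disease-free survival are counted from the allocation visit (a landmark analysis), in line with the visit calendar. Keep registration as the origin for survival of the whole enrolled cohort only.
- **Events before allocation.** State under Statistical analysis how deaths and progressions before the allocation visit are handled. With the landmark they contribute to the whole-cohort curve and not to either arm.
- **Event definition.** Reconcile the secondary objectives with Safety and efficacy on whether distant metastases that can be resected with curative intent are events, and use one definition in both places.

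The cost is a change of wording: registration and allocation are both dated study steps. If the narrower event definition is kept, the outcome form must also record whether each metastasis was resectable with curative intent. Sample size, visits and stopping rule do not change.
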